**Discussion:**

This trial will provide novel information on the possibility of continuing anticoagulant therapy during PPV. The benefits expected from the change in the current surgical management paradigm for anticoagulated patients would be a decreased risk in the incidence of perioperative thromboembolic events and the possibility of performing surgery without delay and without the need for patients to change their usual anticoagulation protocol to the more complex and less safe substitutive therapy.

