So far, no trial has compared the perioperative complications and visual results associated with continuation or interruption of oral anticoagulant therapy before PPV under retrobulbar anaesthesia in a prospective and randomised manner. There is only one study that has evaluated this issue in a prospective but nonrandomised manner, but the authors included a small number of patients, did not standardise the management of anticoagulant agents in the perioperative period and did not record all haemorrhagic complications [11]. Moreover, there is only one study that has evaluated haemorrhagic intraoperative complications associated with PPV in patients under treatment with novel anticoagulant therapy [10].

In order to overcome the shortage of works on this topic, we have designed a randomised clinical trial aimed at comparing haemostasis-related perioperative complications of PPV in patients maintaining anticoagulant therapy before surgery compared to patients who have interruption of this therapy before PPV. Additionally, both the incidence of systemic thromboembolic events after PPV and the changes in visual results after PPV will be compared between the groups.

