### Secondary objectives

Our secondary objectives are to compare changes in the visual results 3 months after PPV in patients who maintain anticoagulant therapy compared to those with interruption of this therapy before surgery and to compare the incidence of systemic thromboembolic events after PPV in those patients who maintain anticoagulant therapy compared to those with interruption of this therapy before surgery.

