### Study arms

In the control group (representing the standard of care), anticoagulant therapy will be interrupted before surgery and patients will receive substitutive treatment with subcutaneous enoxaparin in accordance with the currently employed protocol in the hospital.

To establish substitution therapy, the thrombotic risk of patients is evaluated, taking into account their clinical characteristics. Their renal function is also evaluated by measuring the glomerular filtration rate. In patients undergoing treatment with acenocumarol, if the thrombotic risk is low, they will be treated with enoxaparin 40 mg/24 h; if the thrombotic risk is high and the glomerular filtration rate is less than 30 ml/min, they will be treated with enoxaparin 40 mg/24 h; if the thrombotic risk is high and the glomerular filtration rate is greater than 30 ml/min, they will be treated with enoxaparin 40 mg/12 h. In patients undergoing treatment with the new direct action oral anticoagulants, if the glomerular filtration rate is less than 50 ml/min or if the thrombotic risk is high, the treatment is replaced 5 days before with enoxaparin 40 mg/24 h. If the glomerular filtration rate is greater than 50 ml/min and the thrombotic risk is low, anticoagulant treatment is suspended without the need for substitution treatment.

For the intervention group oral anticoagulant therapy will not be interrupted. Patients will continue their regular oral anticoagulant therapy before and after surgery.

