### Primary and secondary endpoints

The primary endpoint is the presence of any of the following complications: 1) retrobulbar or peribulbar haemorrhage after local anaesthesia (preoperative complication); 2) choroidal haemorrhage or incoercible haemorrhage in the anterior chamber or vitreous cavity during surgery (intraoperative complications); and 3) during the first 2 weeks after surgery, anterior chamber haemorrhage, vitreous haemorrhage, intraretinal haemorrhage or choroidal haemorrhage (postoperative complications). These haemorrhagic complications can be divided according to their clinical relevance into major (choroidal haemorrhage and retrobulbar or peribulbar haemorrhage) and minor (anterior chamber haemorrhage, vitreous haemorrhage and intraretinal haemorrhage). The secondary endpoints are: 1) a change in the corrected visual acuity after surgery (measured as the difference between baseline and 3 months after surgery, in the decimal scale and converted into logMAR scale); 2) thromboembolic events during the first 3 months after surgery; and 3) other surgical procedure-related complications during the first 3 months after surgery.

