## Discussion

Vitreoretinal surgery in anticoagulated patients is a complex situation in which retinal surgeons have to choose between being faced with the systemic thromboembolic risks that the interruption of anticoagulation involves, or the intra- and postoperative haemorrhagic risks associated with maintenance of this therapy.

The interruption of anticoagulant therapy before surgery is not innocuous. The risk of thromboembolic events is increased after this treatment is interrupted and during the interval after its re-instauration, when the International Normalised Ratio is below therapeutic levels. The risk associated with the interruption of anticoagulant therapy oscillates between 0.02% in low-risk patients with atrial fibrillation and 0.42% in high-risk patients with artificial heart valves [12]. Cases of serious complications, and even death, have been described in patients who had interrupted anticoagulant treatment before surgery [13–15]. Some investigators have also suggested that anticoagulant therapy interruption could produce a rebound hypercoagulability state due to the alteration of the balance between vitamin K-dependent factors and proteins C and S [16–19]. Moreover, it is a situation that makes it necessary to postpone surgery for a number of days, and this can compromise visual recovery in some surgical indications such as retinal detachment.

There are only a few studies that have evaluated the possibility of anticoagulant therapy continuation before PPV, and most of the authors agree that this circumstance does not involve a particular risk for patients [5–10]. In this respect, Brown and Mahmoud did not find either intraoperative or postoperative complications attributable to the anticoagulation in 27 eyes undergoing diabetic PPV [5]. Chandra et al. did not find an increase in perioperative or postoperative complications of PPV, in particular haemorrhage, in 60 patients taking warfarin [6]. Fu et al. had good visual results in 25 patients undergoing PPV while on warfarin therapy, with only one highly myopic patient suffering a submacular haemorrhage, which resolved spontaneously with a good final visual acuity [7]. Mason et al. describe one transient vitreous haemorrhage (1.6%) among 64 PPVs performed on patients anticoagulated with warfarin, without significant differences from a control group of 110 individuals [8].

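### The secondary thromboembolic endpoint starts at surgery, so it leaves out the pre-operative days when only the control arm is off its oral anticoagulant

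*Protocol article*

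**What the plan says.** The section Primary and secondary endpoints lists as its second secondary endpoint "thromboembolic events during the first 3 months after surgery". The other statements agree. Secondary objectives: "to compare the incidence of systemic thromboembolic events after PPV in those patients who maintain anticoagulant therapy". Background: "both the incidence of systemic thromboembolic events after PPV and the changes in visual results after PPV will be compared between the groups". The section on participants and procedures also describes follow-up for complications and adverse effects as beginning after the operation. Since all the statements agree, this is a settled definition and not a slip in one sentence.

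Treatment in the two arms diverges earlier. Under Study arms, the control group is described thus: "anticoagulant therapy will be interrupted before surgery and patients will receive substitutive treatment with subcutaneous enoxaparin". For direct anticoagulants, when renal function is reduced or thrombotic risk is high, "the treatment is replaced 5 days before with enoxaparin". Direct-anticoagulant patients with better renal function and low thrombotic risk stop with no substitute. No interval before surgery is given for them or for acenocumarol patients. The intervention arm continues throughout.

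On when the risk arises, the Discussion says: "The risk of thromboembolic events is increased after this treatment is interrupted and during the interval after its re-instauration". The benefit expected from continuation, in the Abstract and again in the Discussion, is "a decreased risk in the incidence of perioperative thromboembolic events".

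**The concern.** Randomisation takes place at the end of screening, before surgery, and the control strategy begins with a pre-operative interruption. The endpoint clock starts only at surgery. The counting rule is the same in both arms but the exposure is not: in the uncounted days only the control arm is off its usual drug. Any excess of events caused by the interruption in those days would fall in the control arm and be left out.

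The definition also makes the count depend on something that happens after randomisation, namely having the operation. A patient whose pre-operative event led to surgery being cancelled has no post-operative period in which an event could be counted.

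This is the endpoint that tests the article's main reason for continuing anticoagulation. The primary endpoint measures the bleeding cost of continuation, and it does include a pre-operative component (haemorrhage after the local anaesthetic). The thromboembolic endpoint measures the cost of interruption and has no such component. A reader weighing the two would see the first from its start and the second only in part.

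**Working it through.** **Plan's own figure.** The article gives no event rate or sample size for the thromboembolic endpoint. Its 48 per arm belongs to the primary endpoint. It is reproduced here only because it is the denominator used below:

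n = (z₀.₉₅ + z₀.₈₀)² × 2 × p(1 − p) / margin² = (1.645 + 0.842)² × 2 × 0.96 × 0.04 / 0.10² ≈ 47.5, rounded up to 48.

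This matches at one-sided 5%; one-sided 2.5% gives 61. Nothing in the present point changes this number.

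**Windows side by side.**

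| Period | Control arm | Intervention arm | Counted by the endpoint? |
|---|---|---|---|
| Randomisation to start of interruption | usual anticoagulant | usual anticoagulant | no |
| Start of interruption to surgery | off the oral anticoagulant; on enoxaparin, or on nothing in one subgroup | usual anticoagulant | **no** |
| Surgery to re-instauration | off the oral anticoagulant | usual anticoagulant | yes |
| Re-instauration to 3 months | usual anticoagulant resumed | usual anticoagulant | yes |

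The second row is the defect: the arms differ, the article's own text says risk is raised, and the endpoint does not look.

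**Expected number of events.** The Discussion quotes a risk associated with interruption of 0.02% (atrial fibrillation, low risk) to 0.42% (artificial valves, high risk). For 48 control patients:

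- 48 × 0.0002 = 0.0096, about 0.01 events; chance of at least one = 1 − (1 − 0.0002)⁴⁸ ≈ 1%.
- 48 × 0.0042 = 0.2016, about 0.20 events; chance of at least one = 1 − (1 − 0.0042)⁴⁸ ≈ 18%.

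**Can the uncounted share be calculated?** As a share of calendar time it is small where the 5 days apply: 5/(5 + 84) = 5.6% with 12 weeks of follow-up, or 5/(5 + 90) = 5.3% taking 3 months as 90 days. What matters is the share of the interruption period. If d is the number of post-operative days before treatment resumes, and risk is constant while interrupted, that share is 5/(5 + d). The document does not give d. Assumed values of 1, 3, 5, 7 and 10 days give 83%, 62.5%, 50%, 42% and 33%. A range this wide, resting on an unstated d, a constant-risk assumption and a 5-day figure that covers only some control patients, is not an estimate. It shows only that the uncounted part need not be trivial.

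**The case against.** The strongest reply has five parts.

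*Pre-operative events would still be recorded.* A reader might infer that they are lost altogether. The document does not support that. The Safety section requires adverse events possibly linked to trial procedures to be recorded and notified during the study period, and a stroke during an assigned interruption would plausibly qualify. The assessment schedule is in figures that are not shown, so what is collected before surgery cannot be judged. What remains is that nothing places such events in the between-group comparison.

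*Leaving the trial is not stated.* A reader might infer that a patient with a pre-operative event would drop out. No rule says so. The narrower point needs no such rule: without surgery, a window defined as following surgery does not exist.

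*The size is easily overstated.* It is tempting to say that half or more of the at-risk time is missed, or that 0.2 control events are expected. The first rests on assumed durations and uniform risk, and applies a 5-day interval stated only for substituted direct anticoagulants to the whole arm. It also treats days on enoxaparin as fully at risk. The second takes only the top of the quoted range, although the Background calls atrial fibrillation the most frequent indication. Patients in whom the anaesthetist finds interruption contraindicated are also excluded. These criticisms stand, and the point is stated without those figures.

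*The bias is conservative.* It works against continuation, so it cannot create a false claim of benefit for the experimental arm on this endpoint. That is true, but the endpoint would still misstate the harm of standard care, and similar counts in the two arms could be read as showing no benefit of continuation.

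*The endpoint is secondary and cannot be powered with either window.* This is also true, and the article acknowledges small numbers and a low expected incidence of complications. It limits how much the point matters but does not make the definition correct.

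**Conclusion.** The point holds in a limited form. As defined consistently in three places, the thromboembolic endpoint omits part of the period in which the arms are treated differently and in which the article itself says risk is raised. The omission bears on the control arm and biases the comparison against showing the benefit of continuation. A pre-operative event may appear in the safety record but not in the comparison.

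The absolute size is small: 0.01 to 0.20 expected events across 48 control patients, if the quoted interruption risks apply to this population. The uncounted fraction of those events cannot be derived from the document. The primary endpoint, its margin and the sample size are unaffected. This is a fault in the validity of a secondary endpoint, worth correcting because with so few events one uncounted event could be the trial's whole thromboembolic signal.

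**What to change.** Redefine the endpoint as any systemic thromboembolic event from randomisation, in all randomised patients whether or not they are operated on, over a window of the same length in both arms. Use the same wording in the Background, Secondary objectives and Primary and secondary endpoints.

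Moving only the start is not enough. The Background and Discussion say that interruption postpones surgery, so a window from randomisation to 3 months after surgery could observe control patients for longer and add control events through observation time alone. A fixed period from randomisation, long enough to cover the 3-month visit, avoids this. The article does not give the time from randomisation to surgery, so the team must set that length. If the time to surgery differs between arms and a fixed window is impractical, events per person-time are the alternative. They are weaker here, because the risk is not expected to be constant over the window.

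The cost is low. The anaesthetist already checks before surgery that the assigned anticoagulant procedure was followed (section Pars plana vitrectomy), and one question on pre-operative events can be added there in both arms. Patients who are not operated on need a few follow-up contacts. Sample size, treatment and clinical management do not change.

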### Safety

All adverse events and serious adverse events which might be related to the study procedures will be recorded, investigated and notified to the regulatory authorities and to the ethics committee by the researchers during the study period, in accordance with Clinical Trials Directive 2001/20/EC.

### Finalisation or interruption of the study

The trial will be considered finished when all the patients have concluded the follow-up period. It may be interrupted under any of the following situations: 1) impossibility of recruiting the number of patients previously determined; 2) noncompliance with the requisites of the protocol; 3) noncompliance with the rules of clinical practice or current legislation; and 4) appearance of unexpected risks that are unacceptable for patients.

### Statistics

#### Sample size

Considering that there is no difference in the probability of not having complications between the standard therapy (anticoagulant interruption) and the experimental therapy (no interruption of anticoagulant), and assuming a 95% confidence level and a 96% probability of not having complications, 48 patients are required in each arm (*n* = 48 × 2) in order to have an 80% probability that the upper limit of the confidence interval excludes a difference of over 10% in favour of the standard group. Calculations are performed by Sealed Envelope Ltd.

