### Hypothesis

We hypothesise that anticoagulant therapy maintenance before PPV is not associated with a significant increase in perioperative complications compared to those cases in which this therapy is interrupted before surgery, and that the postoperative visual results are not inferior in those cases in which anticoagulant therapy is maintained compared to those cases in which such therapy is interrupted before surgery.

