Even though some authors have found an increased risk of haemorrhagic complications in anticoagulated patients undergoing PPV, the incidence has been low, without statistical significance, and without serious consequences for visual acuity [9–11, 20, 21]. Dayani and Grand analysed 54 patients who underwent PPV while taking warfarin and found four patients who suffered postoperative vitreous haemorrhage, all of which resolved spontaneously requiring no further surgery [9]. Grand and Walia studied 36 eyes of 33 patients who underwent PPV while being treated with novel anticoagulant therapy and reported that four eyes (11.1%) experienced postoperative vitreous haemorrhage after which two eyes (5.5%) required repeat surgical intervention and two eyes (5.5%) cleared spontaneously [10]. Meillon et al. [11] and Oh et al. [20] report 6.6% and 7% of haemorrhagic complications, respectively, after PPV in patients undergoing anticoagulation therapy, in both studies without visual consequences in the long term. Narendran and Williamson report one case of postoperative choroidal haemorrhage, but only 7 of the 541 patients in their study were taking warfarin during PPV [21].

In contrast to other eye surgeries, vitreoretinal surgery has been considered to pose a high haemorrhagic risk [22]. This means that any perioperative bleeding could have devastating consequences. However, according to the current scientific evidence, this statement cannot be considered to be strictly true. The minor haemorrhagic complications (anterior chamber haemorrhage, vitreous haemorrhage and intraretinal haemorrhage) that can be expected after PPV have a minimal clinical relevance and spontaneous resolution without long-term consequences is usually the norm, with the systemic risk from anticoagulant therapy interruption being much greater. The major haemorrhagic complications are very rare. Most choroidal haemorrhages resolve spontaneously, although some cases with massive haemorrhage and retinal apposition may be difficult to manage. With regard to retrobulbar haemorrhages, they also resolve spontaneously, although their appearance may cause the surgical intervention to be delayed. This circumstance has led to many authors proposing a change in this paradigm and considering PPV as having moderate or even low haemorrhagic risk and considering continuing anticoagulant therapy before surgery [23–25], an assertion that the present trial will attempt to assess.

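### Meeting the 10-point margin, set on an assumed 4% complication rate, excludes only a 10-point excess: it does not support a conclusion of no significant increase and says little about major haemorrhage

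*Protocol article*

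**What the plan says.** The protocol article, Sample size, takes it that "there is no difference in the probability of not having complications between the standard therapy" and continuation, "assuming a 95% confidence level and a 96% probability of not having complications". It asks for 48 patients per arm so that there is an "80% probability that the upper limit of the confidence interval excludes a difference of over 10% in favour of the standard group". The section does not say whether the interval is one- or two-sided, or which method gives it. No section of the article gives a reason for 10 points.

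The Hypothesis section is worded differently. It states that "anticoagulant therapy maintenance before PPV is not associated with a significant increase in perioperative complications", relative to interruption.

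Primary and secondary endpoints defines one composite of any haemorrhagic complication. It sorts the components into major (choroidal, retrobulbar or peribulbar) and minor (anterior chamber, vitreous, intraretinal), but all count alike towards the primary endpoint.

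Data analysis, as printed, gives haemorrhage incidence by arm with 95% intervals, and adjusted odds ratios if baseline characteristics differ. It does not tie the conclusion to the upper limit of the between-arm difference. One sentence in that section looks garbled, so some words may have been lost.

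**The concern.** The calculation and the hypothesis make different promises. The calculation sizes the trial to exclude an excess of 10 points or more. The hypothesis reads as if a successful trial would show that continuing anticoagulation does not raise the complication rate.

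The gap matters because the margin is large relative to the assumed rate. An excess of a few points would be a sizeable relative increase here, yet it lies well inside what the margin tolerates. The Discussion looks ahead to a change in how anticoagulated patients are managed for vitrectomy, so a pass reported as no increase could carry more weight than it can bear. That applies most to the major haemorrhages, which are rare and are pooled with minor ones.

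**Working it through.** **Inputs.** All are from Sample size: complication rate 4% in both arms (from "96% probability of not having complications"), true difference 0, margin 10 points, 95% confidence, 80% power, 48 per arm.

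**1. Reproducing 48 per arm.** With unpooled variance,

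n = [p0(1−p0) + p1(1−p1)] × (z_α + z_β)² / margin² = (2 × 0.04 × 0.96) × (z_α + 0.842)² / 0.10².

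- One-sided 5% (z = 1.645): 0.0768 × 6.183 / 0.01 = 47.5, so 48. This matches.
- Upper limit of a two-sided 95% interval (z = 1.960): 0.0768 × 7.849 / 0.01 = 60.3, so 61. This does not match.

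The stated figure therefore corresponds to a one-sided 95% limit, although the article does not say so.

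**2. What the margin means.**

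- Margin / assumed rate = 10 / 4 = 2.5.
- Boundary of the tolerated region = 4% + 10 points = 14%, which is 14 / 4 = 3.5 times the assumed rate.

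**3. How often a trial of 48 per arm would meet the margin.** I summed the product of the two binomial probabilities (n = 48 each) over all pairs of event counts for which the upper limit of the risk difference is below 0.10. The control rate is 4% throughout. The score limit is the restricted-likelihood one.

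| True rate on continuation | One-sided 95%: Wald / Newcombe / score | Two-sided 95%: Wald / Newcombe / score |
|---|---|---|
| 4% (no harm) | 81% / 72% / 64% | 76% / 49% / 49% |
| 6% (1.5-fold) | 60% / 49% / 42% | 52% / 29% / 29% |
| 8% (2-fold) | 40% / 30% / 26% | 32% / 16% / 16% |
| 14% (boundary) | 7% / 5% / 4% | 5% / 2% / 2% |

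The one-sided Wald figure at 4% v 4% (81%) agrees with the planned 80%.

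Hand check of the 6% row, one-sided, by normal approximation: SE = √[(0.04 × 0.96 + 0.06 × 0.94)/48] = √(0.0948/48) = 0.0444; (0.10 − 0.02)/0.0444 − 1.645 = 0.155; Φ(0.155) = 56%, close to the exact 60%.

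**4. Major haemorrhage.** Even with no major bleed among 48 patients on continuation, the exact one-sided 95% upper limit for that arm is 1 − 0.05^(1/48) = 0.0605, about 6%. That exceeds the 4% assumed for major and minor bleeds together.

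**The case against.** Four points can fairly be made for the plan.

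- **A margin is a trade-off, and passing at a small true excess is how any non-inferiority design works.** This stands. A 2-point excess is inside a 10-point margin by construction, so the 6% row shows what the margin permits and is not a miscalculation.
- **The article condenses a longer protocol, available on request, which may justify the 10 points.** This also stands. The absence noted here is from the article only.
- **The Discussion argues that minor bleeds matter little and lists small numbers and low incidence as limitations, and Data analysis reports incidence by arm.** This stands in part. The argument is never linked to 10 points and does not extend to the major events. The limitation is framed as difficulty in reaching significance, not as a limit on what a pass would show.
- **The hypothesis is not a reporting rule.** True, but it is the article's statement of what the trial expects to show on the primary endpoint, and the sample size supports a weaker statement. If a significant increase was meant as one beyond 10 points, the text should say so. If it was meant as statistical significance, a non-significant difference in 96 patients would not show that there is none.

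A reader might also infer more than the documents support:

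- **That a rise to nearly 14% would usually be passed as non-inferior.** It would not: 14% is the boundary, and a true rate there passes about 2% to 7% of the time.
- **That a 1.5-fold harm passes more often than not.** In the table this is so only with the Wald limit, and the article names no method.
- **That the article's own figures prove the margin too wide.** The highest cited rate ("four eyes (11.1%) experienced postoperative vitreous haemorrhage after which two eyes (5.5%) required repeat surgical intervention") comes from 36 eyes with no comparison rate given, so subtracting an assumed 4% does not estimate an effect of continuation. Nor can 10 points simply be set against the thromboembolic risk, which "oscillates between 0.02% in low-risk patients with atrial fibrillation and 0.42% in high-risk patients with artificial heart valves". The events differ in severity, and the article also names surgery without delay and avoiding substitutive therapy as benefits.

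**Conclusion.** The point holds as a mismatch between the margin and the claim; it does not show that 10 points is the wrong margin. Meeting the criterion would exclude an absolute excess of 10 percentage points or more and nothing smaller. It would not support a conclusion of no significant increase, and it would say little about choroidal, retrobulbar or peribulbar haemorrhage.

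The 14% ceiling and the pass probabilities assume a true 4% rate on interruption and 48 evaluable patients per arm. The range of 29% to 60% at a true 6% reflects the unstated interval method and sidedness. The 60% end belongs to the one-sided Wald rule, the setting that reproduces the planned sample size.

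**What to change.** Keep the 96 patients and the 10-point margin. At the same 4% rate, one-sided 5% and 80% power, a 5-point margin would need 0.0768 × 6.183 / 0.05² = 190 per arm, so matching the claim to the margin is the practical course.

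1. **Hypothesis.** Reword it so that the conclusion on success is that an absolute increase of 10 percentage points or more is excluded. State that meeting the margin will not be reported as no increase.
2. **Data analysis.** Make the upper confidence limit of the between-arm risk difference for the composite the primary result, judged against 10 points.
3. **Major haemorrhage.** Report choroidal, retrobulbar or peribulbar haemorrhage separately by arm with exact intervals. State that meeting the composite margin does not establish non-inferiority for these events, since even 0/48 leaves an upper limit of about 6%.

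The cost is wording in two sections and one extra table row, with no added patients or procedures. The downside is a more modest headline claim.
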